### 2.8. Sample Size Calculation

Given the novelty of the study, the sample size was estimated indirectly with reference to the relevant CM literature as reviewed by the UK National Institute of Care Excellence (NICE Clinical Guideline 51; Appendix 15 [56]. The study was powered for 80% to detect a difference of 3 weeks opioid abstinence as evaluated by NICE for three trials (an odds ratio in favour of CM of 2.56; 95% CI 1.76 to 3.72). Using this pooled effect, uplifted by 15% for attrition and with a 5% two-sided alpha, it was estimated that 92 participants should be allocated to the experimental and control group.

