## 2. Methods

### 2.1. Study Design, Population, and Setting

The Suboxone Treatment and Recovery Trial (STAR-T) is a single centre, 16-week outpatient intervention, two-arm, pragmatic, phase IV randomised controlled trial of OAT and adjunctive TDM for OUD. The study population is adults (≥ 18 years) with current OUD.

The study setting is the specialist OUD treatment and care programme operated by National Rehabilitation Centre (NRC), Abu Dhabi, United Arab Emirates (UAE; www.nrc.ae). In the UAE, use and combination use of heroin, morphine, and illicit tramadol are the most prevalent [29, 30]. The NRC treatment programme includes an inpatient unit for assessment and management of medical and mental health comorbidities with (poly) substance and alcohol use disorders [29–31]. In 2002, the NRC introduced OAT with BUP with induction and stabilisation procedures conducted in the inpatient unit. However, following concerns about medication diversion in 2011, the NRC suspended all new admissions to OAT pending the development and findings from the present study.

Following a standard of care protocol for OAT, all participants will first complete inpatient care (up to four weeks) to achieve medically supervised withdrawal and stabilisation on BUP/NX-F and to estimate the BUP Elimination Rate (EL.R). After study enrolment and prior to discharge, participants will be randomly allocated (1:1: using an online randomisation service [32] with no stratification) to an experimental group (that immediately received 16 weeks of outpatient BUP/NX-F maintenance, standard case management, and manualised adjunctive medication management with TDM monitoring and CM) or to a treatment-as-usual, control group (that immediately received BUP/NX-F and standard case management and usual medication management only). Using ongoing medication management, TDM, and CM protocol, participants in the experimental group will be able to receive up to four weeks of medication on a take-home basis. All participants will continue to receive ongoing treatment after 16 weeks as usual.

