#### 2.6.4. Interventions for the Control Group

Participants randomised to the TAU control group will receive BUP/NX-F dosing according to preference of daily, twice weekly, or every two weeks alternatives without a mandatory supervised dosing period. In this group, take-home doses will be provided contingent on provision of negative UDS only without following a fixed protocol. Medication management sessions will not be delivered according to structured manual and no monitoring of BUP levels will be done.  Table 3 contrasts the interventions under the experimental and control group.

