### 2.7. Study Outcomes

#### 2.7.1. Primary Outcome

The primary outcome measure for the study will be the count of negative opioid UDS (excluding BUP) over 16 weeks. Scheduled appointments for a UDS that are missed will be conservatively imputed as positive for opioids.

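### The stated 80% power belongs to a yes/no abstinence endpoint that the trial does not analyse, and the text does not say whether 92 is per arm or in total

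*Protocol article*

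**What the plan says.** All references are to the protocol article.

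- Section 2.8 explains that "the sample size was estimated indirectly with reference to the relevant CM literature". The power claim is: "The study was powered for 80% to detect a difference of 3 weeks opioid abstinence as evaluated by NICE for three trials". The effect is given as "an odds ratio in favour of CM of 2.56; 95% CI 1.76 to 3.72", the other inputs as "uplifted by 15% for attrition and with a 5% two-sided alpha", and the result as: "it was estimated that 92 participants should be allocated to the experimental and control group". No control-arm rate, mean or standard deviation is given.
- Section 2.7.1: "The primary outcome measure for the study will be the count of negative opioid UDS (excluding BUP) over 16 weeks". The Abstract gives the primary outcome as a mean percentage of negative screens over the same period. Missed scheduled screens count as positive.
- Sections 2.7.2 and 2.7.3 list retention, change in psychosocial functioning, and correlations with the outcomes. A three-week abstinence endpoint appears nowhere.
- Section 2.9 plans a fixed-effects logistic model for the primary outcome and a t-test or Mann-Whitney test between groups, by intention to treat.
- Section 2.1 sets 1:1 allocation. In the control arm, Section 2.6.4 says that "take-home doses will be provided contingent on provision of negative UDS only without following a fixed protocol".

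**The concern.** A power statement tells the reader what the primary analysis can be expected to detect. Here the outcome sized and the outcome analysed differ. The logistic model does not close the gap: applied to screens, it estimates the odds that a screen is negative, not the odds that a participant is abstinent for three weeks.

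The second problem is the number itself. The sentence giving 92 can be read as a total or as a figure for each arm, and the two readings differ by roughly 30 points of power on the plan's own effect. A reader who takes 92 as the total is told 80% when the inputs cannot give it.

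At stake is how the result is read. If the difference in negative screens is not significant, the 80% invites the conclusion that a clinically relevant effect has been ruled out, although no calculation on that outcome supports this.

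**Working it through.** **Inputs from Section 2.8:** OR 2.56, two-sided alpha 5%, power 80%, attrition uplift 15%, result 92. **From Section 2.1:** 1:1 allocation. **Assumed, because not stated:** the control rate p0, scanned from 0.02 to 0.95.

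**1. Formulae.** The rate in the experimental arm is p1 = 2.56·p0 / (1 − p0 + 2.56·p0). The pooled two-proportion size per arm, with p̄ = (p0 + p1)/2, is

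n = [1.96·√(2p̄(1 − p̄)) + 0.8416·√(p0(1 − p0) + p1(1 − p1))]² / (p1 − p0)².

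**2. Reproducing 92.** It comes back as a per-arm figure, but from more than one control rate:

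| Formula | Uplift | p0 | n per arm | After uplift |
|---|---|---|---|---|
| Pooled | ×1.15 | 0.25 (p1 = 0.460) | 80.0 | 92.0 |
| Pooled | ×1.15 | 0.54 | 80.0 | 92.0 |
| Pooled | ÷0.85 | 0.265 | 78.2 | 92.0 |
| Pooled | ÷0.85 | 0.52 | 78.2 | 92.0 |
| Log odds ratio | ÷0.85 | 0.30 | 77.9 | 91.7 |
| Log odds ratio | ×1.15 | 0.50 | 79.5 | 91.4 |

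The last two rows use n = (1.96 + 0.8416)²·[1/(p0q0) + 1/(p1q1)] / (ln 2.56)², with q = 1 − p. The control rate used by the authors therefore cannot be recovered from 92.

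**3. Can 92 be the total?** That would be 46 per arm, or 39 to 40 before uplift (46 × 0.85 = 39.1; 46/1.15 = 40). The smallest n at any control rate is 72.5 per arm (near p0 = 0.385), or 83.4 with ×1.15 and 85.3 with ÷0.85. So no control rate gives 92 as a total.

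**4. Power for OR 2.56 under each reading** (two-sided 5%; 92 × 0.85 = 78.2 evaluable per arm):

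| p0 | 92/arm | 78/arm | 46/arm | 39/arm |
|---|---|---|---|---|
| 0.10 | 61% | 54% | 35% | 31% |
| 0.20 | 81% | 75% | 52% | 45% |
| 0.25 | 85% | 79% | 56% | 49% |
| 0.40 | 89% | 83% | 60% | 53% |
| 0.50 | 87% | 81% | 58% | 51% |
| 0.70 | 73% | 66% | 44% | 38% |

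Over the whole scan, 46 per arm peaks at 60.3% and 39 at 53.2%. With 78 per arm, power is at least 80% for p0 from 0.267 to 0.517, with a maximum of 83%.

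**5. The outcome that is analysed.** Without a mean or SD, power on the count or percentage cannot be computed, but the detectable difference in SD units can. The normal approximation is d = (1.96 + 0.8416)·√(2/m):

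- m = 92: 0.413, or 0.415 with the t distribution. For an assumed SD of 30 to 40 percentage points this is 12.5 to 16.6 points.
- m = 78: 0.449, or 0.451 with the t distribution, which is 13.5 to 18.1 points.
- m = 46 and m = 39 (92 as the total): 0.584 and 0.634.

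**The case against.** The strongest defence is that the section is open about its method: it calls the estimate indirect and gives the novelty of the study as the reason. On the per-arm reading nothing is miscalculated, since 92 reproduces. A journal article may also leave the control rate to the full protocol. All of this stands. The missing rate is not a defect in itself; it matters here because the 80% cannot be checked without it. But disclosing a proxy does not turn its power into the power of the primary analysis, and the per-arm question is one of wording that the printed sentence leaves open.

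A reader might infer four stronger things that the documents do not support:

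- **That the control rate was 25%.** It reproduces 92, but so do several other rates.
- **That the trial is underpowered on its primary outcome.** This is not shown. Converting OR 2.56 to a standardised difference (ln 2.56 × √3/π = 0.52) gives 94% power with 92 per arm and 90% with 78. That conversion is itself an assumption, so power on the screens outcome is unknown, not known to be low.
- **That the odds ratio compares contingency management (CM) with none and so overstates this trial's contrast.** The comparators in the three pooled trials are not described. The control arm does have take-home doses contingent on negative screens, which could shrink the effect. The experimental arm adds drug monitoring, supervised dosing and manualised sessions, which could enlarge it. The direction cannot be settled; only that the effect may not carry over.
- **That low power at the lower confidence limit, OR 1.76, is an error.** A trial need not be powered at that limit.

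**Conclusion.** The point holds in two parts.

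First, the 80% is a statement about a binary three-week abstinence endpoint outside the planned outcomes, so it is not a property of the primary analysis. The phrase about a difference of three weeks is loose, but the only effect size given is an odds ratio, so the calculation is binary. This part follows from the text alone.

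Second, the 92 is ambiguous, and the ambiguity decides the claim. As a total, it cannot support 80% at any control rate under the stated inputs. As a per-arm figure, it can, but that reading is necessary and not sufficient: after 15% loss the control rate must also lie within the range found above. These figures rest on the pooled two-proportion formula without continuity correction.

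The detectable differences in SD units need no control rate. Their translation into percentage points rests on the assumed SD of 30 to 40. Using all 92 per arm fits intention to treat with missed screens counted as positive; using 78 fits an analysis that loses 15%.

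This should be corrected, but it is a matter of reporting and gives no ground for changing the size of the trial.

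**What to change.** Reword Section 2.8:

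1. State that 92 is per arm, 184 in total. If 92 is in fact the total, withdraw the 80% and state that power for OR 2.56 is at most about 60%.
2. Report the control-arm rate actually used. Only the authors can supply it; 25% should not be inserted because it happens to fit.
3. Label OR 2.56 as a proxy taken from CM trials on a binary abstinence endpoint. Note that this control arm also has take-home doses contingent on negative screens, so the effect may not carry over.
4. Replace the 80% claim for the primary outcome with the detectable difference on that outcome. At 92 per arm and 80% power this is 0.415 SD if all are analysed with missed screens imputed positive, or 0.45 SD with 78 per arm. Give it in percentage points (12.5 to 16.6, or 13.5 to 18.1) only with the SD of 30 to 40 marked as assumed. If 92 is the total, use the figures for 46 and 39 per arm, about 0.58 and 0.63 SD.

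The cost is a few sentences. Enrolment, outcomes and analysis stay as they are. Section 4 says data analysis is still in progress, so the correction is best made before results are reported.

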### 2.9. Statistical Analysis of the Primary and Secondary Outcomes

Data for the whole population and by study group will be analysed for mean, standard deviation, 95% confidence interval, and range. With no interim analysis, all statistical analyses will be pragmatically done according to intention-to-treat principle. All analyses will be conducted using two-sided 5% significance test. A fixed-effects logistic model will be applied to analyse the primary outcome. To analyse between group differences, student* t*-test will be conducted for normally distributed data, or a Mann-Whitney test. For the primary outcome, a planned sensitivity analysis will determine the impact of the imputed or complete case [57]. Alternatively, reported observed opioid screens or actual screens without imputation will be analysed between group differences. Secondary outcome will be evaluated using proportional hazards regression model and Chi-Square test will be performed to measure between group differences.

### 2.10. Analyses for Exploratory Outcome

Bivariate correlation tests to explore correlations with study outcomes will be performed. Specifically, Pearson's correlation will be applied for continuous and Spearman's rho test for categorical data. Factors demonstrating significant correlation and those with potential impact on the primary outcome will be studied for predictive power using a simple linear regression model. Finally, analysing for the effect of confounders will be done using univariate analyses for factors generating higher correlation (>0.5). The mean change from baseline scales or within group change will be analysed using a generalised linear model framework. A paired* t*-test will be conducted where normal distribution is assumed or alternatively Kruskal-Wallis test. The magnitude of change from baseline will be estimated using bias corrected Hedge's* g* effect size. Mean difference between groups will be analysed using student* t*-test where normal distribution is assumed or a Mann-Whitney test.

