The Alt-D schedule will be a 3 × 48-hour dose and 1 × 24-hour dose. The TIW schedule will be a 2 × 48-hour dose and 1 × 72-hour dose (calculated as 3 × 24-hour dose at a maximum of 32 mg) [53, 54]. Clinical determination of the dosing schedule was informed by illicit injecting status (i.e., participants injected street heroin/morphine will receive daily doses and noninjected heroin and morphine users received alternate daily doses) while prescription opioid users (nonpolysubstance users) will receive TIW doses. Additionally, participants with severe psychiatric comorbidity, polysubstance use, or a body mass index (BMI) of ≥30 will be placed on the next higher frequency schedule (e.g., from TIW to ALT-D). Fine dose adjustments will be guided by self-report participant comfort, sleeping, craving, and pupil reflexes. Participants continuing to observe craving and or signs of withdrawal will be transferred to the next frequent dosing schedule towards the daily schedule as illustrated by Figure 1.

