#### 2.7.3. Exploratory Outcomes

There is change in psychosocial functioning from baseline at the end of the 16-week treatment. There is correlation of participant demographics, clinical data, BUP EL.R, and BUP/NX-F maintenance dose with the primary and second outcome.

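### Kruskal-Wallis is the wrong fallback for a paired t-test on change from baseline; the rules for categorical factors and confounders in the same section also need tightening (exploratory outcomes only)

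*Protocol article*

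**What the plan says.** Section 2.7.3 of the protocol article lists two kinds of exploratory outcome. One is change in psychosocial functioning from baseline to the end of the 16 weeks. The other is "correlation of participant demographics, clinical data, BUP EL.R, and BUP/NX-F maintenance dose with the primary and second outcome".

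Section 2.10 sets out the analyses:

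- **Change from baseline.** "The mean change from baseline scales or within group change will be analysed using a generalised linear model framework". For the significance test, the section says of the paired t-test that it "will be conducted where normal distribution is assumed or alternatively Kruskal-Wallis test". Hedges' g gives the size of the change. Differences between groups have their own rule in the next lines: Student's t-test, or Mann-Whitney.
- **Correlations.** "Pearson's correlation will be applied for continuous and Spearman's rho test for categorical data".
- **Prediction.** Factors that correlate significantly, or that may affect the primary outcome, "will be studied for predictive power using a simple linear regression model".
- **Confounding.** Then, "analysing for the effect of confounders will be done using univariate analyses for factors generating higher correlation (>0.5").

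Section 2.6.1 describes how patients come to a dosing schedule: "Clinical determination of the dosing schedule was informed by illicit injecting status". Opioid type, psychiatric comorbidity, polysubstance use and body mass index also enter.

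**The concern.** Kruskal-Wallis with two samples is a rank-sum test for independent groups. Applied to baseline and week 16 scores of the same participants, it treats each person as two unrelated people. Scores of one person are usually positively correlated over time, so the test overstates the variance of the comparison. Its true error rate falls below 5% and real change is harder to detect. The section assigns between-group comparisons to other tests, so the Kruskal-Wallis clause cannot be read as one of those.

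Two further rules in the section are looser than they should be.

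- Spearman's rho is given to categorical data without limit. For an unordered factor with three or more levels, rho depends on how the levels happen to be numbered. Section 5 mentions such characteristics: city of residence, and type and pattern of opioid use.
- The sequence of bivariate correlation, simple regression and univariate analyses names no covariate at any step, and the cut-off of 0.5 would pass over moderate confounders. The first exploratory aim in Section 2.2 concerns dose and elimination rate, and patient characteristics that steer treatment may also predict outcome.

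**Working it through.** Section 2.10 states no figure to reproduce, so the check is of how the named tests behave.

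**Inputs from the protocol article**

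- Two-sided 5% tests (Section 2.9).
- 92 participants, read as per group, including a 15% uplift for attrition (Section 2.8). Pairs left at week 16: 92 × (1 − 0.15) = 78.2, about 78 per arm.

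**Assumed inputs (the protocol gives none)**

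- Baseline-to-week-16 correlation ρ of 0.3 to 0.7, with 0.5 as the central case.
- True change of 0 or 0.3 SD.

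**1. Type I error by formula.** With equal numbers at both times, the pairing multiplies the variance of the rank-sum statistic by about 1 − ρs, where ρs is the rank correlation. For bivariate normal data ρs = (6/π) × arcsin(ρ/2). The true rejection rate under no change is 2 × [1 − Φ(1.96/√(1 − ρs))].

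For ρ = 0.5: ρs = 0.483; √(1 − 0.483) = 0.719; 1.96/0.719 = 2.725; rejection rate 0.0064, or 0.6%. For ρ = 0.3 the same steps give 2.0%, and for ρ = 0.7, 0.05%.

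**2. Simulation, 78 pairs, normal data, 3,000 runs per cell**

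| ρ | Type I error, Kruskal-Wallis | Type I error, signed-rank | Power at 0.3 SD, Kruskal-Wallis | Power at 0.3 SD, signed-rank |
|---|---|---|---|---|
| 0.3 | 2.0% | 4.8% | 44% | 58% |
| 0.5 | 0.9% | 4.8% | 43% | 73% |
| 0.7 | 0.1% | 5.3% | 41% | 91% |

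Formula and simulation agree: at ρ = 0.5 the error rate is 0.6% to 0.9%.

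**3. Skewed data.** The fallback applies only when normality is not assumed, so the comparison was repeated on log-normal data (ρ = 0.5, shift of 0.3 SD before transformation). Power is 42% for Kruskal-Wallis against 66% for signed-rank; type I error is 0.8% against 4.8%. Kruskal-Wallis uses only ranks, so a common monotone transformation leaves it unchanged apart from simulation noise.

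**4. Spearman's rho.** In one simulated factor with three unordered levels (52 per level, 156 in all), renumbering the levels moves rho from 0.02 (p = 0.77) to 0.32 (p < 0.001) on the same data. For a two-level factor there is no such problem: p = 0.0134 for Spearman and 0.0140 for Mann-Whitney.

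**5. Confounding.** Suppose a factor correlates r with both dose and outcome, and dose has no effect. The induced correlation is r × r: 0.3 × 0.3 = 0.09, and 0.5 × 0.5 = 0.25. With 156 participants (2 × 78), the single-predictor test is significant in 20% of runs at r = 0.3 and 89% at r = 0.5. With adjustment for the factor it is about 5% in both. Neither value of r exceeds the 0.5 cut-off. These strengths are assumptions, and the protocol does not say which correlation the cut-off refers to.

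**The case against.** The best defence is that this is exploratory and partly covered already. The section names a generalised linear model framework and Hedges' g for change from baseline, so Kruskal-Wallis would not be the only evidence. The fallback applies only to non-normal data. Its error is conservative, so it creates no false claim of change. All of that stands, and it limits the weight of the point. It does not make the named test suitable, and the loss persists on skewed data.

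On the secondary points, much of the defence also stands:

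- Spearman's rho is usable for ordinal and two-level factors. Injecting status can be coded in two levels, and the PHQ-9 and GAD-7 bands are ordered. The gap concerns only unordered factors with more levels, and the protocol does not say outright that rho will be computed on these.
- Univariate can mean one dependent variable with covariates allowed. A reader might infer that the plan rules out adjustment; the text does not establish that. It names no covariates, and the simple regression before it suggests one predictor at a time.
- A reader might infer that Section 2.6.1 assigns dose by severity. It assigns the schedule by those characteristics, and refers dose to the 24-hour amount needed to bring the withdrawal score below 5. It does cite published correlations between patient characteristics and maintenance dose as the basis for the regimen, so confounding of dose is plausible but not built in by rule.

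A reader might also infer that both exploratory aims in Section 2.2 would be answered wrongly. The documents do not support this. Those aims are associations with opioid use and retention; change from baseline is a separate outcome in Section 2.7.3, so the Kruskal-Wallis error reaches neither aim.

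**Conclusion.** The Kruskal-Wallis clause is wrong as written and should be corrected. In the central case (78 pairs, ρ = 0.5, 0.3 SD change), it costs about 30 points of power on normal data (73% − 43%) and 24 on log-normal data (66% − 42%). The size rests on the assumed correlation and change. The direction holds for any positive correlation between baseline and week 16, and the loss grows with it.

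The Spearman and confounder rules are secondary: the first needs a limit and the second an explicit model. For these the wording admits a benign reading, and confidence is moderate.

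The reach is narrow. The Kruskal-Wallis error affects the change-from-baseline outcome in Section 2.7.3. The secondary points bear on the exploratory associations. The comparisons between arms on the primary outcome and on retention do not use any of these rules.

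**What to change.** 1. In Section 2.10, or in the analysis plan that implements it, replace Kruskal-Wallis with the Wilcoxon signed-rank test as the alternative to the paired t-test. This is a change of wording and costs nothing.
2. Limit Spearman's rho to ordinal or two-level factors. For unordered factors with three or more levels, such as opioid type or city of residence, use a group comparison (here Kruskal-Wallis is suitable, for a continuous outcome) or a regression with indicator terms.
3. Estimate the associations of dose and elimination rate with each outcome in a multivariable model. Include arm and the characteristics that determine the dosing schedule in Section 2.6.1 (injecting status, opioid type, psychiatric comorbidity, polysubstance use, body mass index), and drop the correlation cut-off. Other prespecified covariate sets are defensible; what matters is that the set is listed and adjustment is explicit.

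The variables in item 3 are already needed to assign schedules, so no new data are required. Section 4 says that data analyses are in progress, so the change should be dated and recorded, and any result already obtained under the present rules should be reported as such.
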